#### Secondary outcomes

Secondary financial outcomes include savings (having enough to cover an unexpected expense of $400) (81); holding of debt (including fraudulent debt, owed child support, banking/overdraft fees, bail debts, school debts, utility debts, and credit card or payday loan debt); credit score; and financial capability, a composite measure of financial knowledge, skills, and practices (45) that is sensitive to rapid change following similar financial capability interventions (82, 83). In addition to self-reported savings and spending, we will utilize aggregated data from the CFR Focus Card to assess spending, balances, and savings by treatment group as well as by engagement in financial capability programming. We will also examine intensity of the measures that comprise the primary financial well-being outcome (time invested in education, certification, and employment training program participation).

Secondary mental health outcomes include moderate or severe anxiety indicated by a score ≥ 10 on the GAD-7 (66, 67) and hope/future orientation measured by the Hope Matters Scale (68, 69). Secondary physical health outcomes include general self-rated health (70) and fatigue (84).

Covariates include: socio-demographic characteristics, including education, employment, income, partnerships, household membership, living/housing situation, and financial supports. We will also assess BEAs’ strengths and assets, and other individual, social and structural contextual factors that could act as potential confounders, could modify the effect of the intervention, or could mediate the intervention’s impact on mental and physical health.

### Analyses

#### Preliminary analyses

Frequency tables for all categorical variables and measures of central tendency and variability for continuous variables (e.g., average monthly income, age) will be used to characterize the sample and check for imbalances between the randomization arms. If arms differ significantly at baseline on one or more covariates or if imbalances in arms occur due to differential loss to follow-up, we will use causal modeling methods (e.g., inverse probability weighting, targeted maximum likelihood estimation) to balance distributions and obtain the desired marginal effect estimates under the counterfactual assumption of balanced arms (85–89). We will address incomplete data with multiple imputation (90). SAS will be used for analyses.

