### Measures

#### Exposure

The primary exposure is intervention arm assignment (see all measure in Table 1). Secondary exposure variables include: receipt of financial mentoring (yes/no) and participation in peer discussion groups (yes/no) during each 3-month study interval. Because engagement with any treatment option will vary by individual, we will also capture intervention dose (e.g., mentoring sessions attended) on study monitoring forms.

**Table 1 tab1:** Study measures: domains, instruments, and time points.

Domain	Instrument/measure	Data source and frequency
Primary exposure		
Intervention	Randomization arm (GI receipt in phase I or phase II)	Study records
Primary outcomes		
Financial well-being	Investments in future (Enrollment in education/training)	Quarterly surveys
Mental Health	CESDR-10: major or probable major depressive episode (64, 65)	Quarterly surveys
Unmet need for health services	Unmet need for mental health services	Quarterly surveys and monthly brief check-ins
	Unmet need for sexual and reproductive health services	Quarterly surveys and monthly brief check-ins
Secondary outcomes		
Financial well-being	Savings, Debt	Surveys at baseline, 6, 12, 18, 24 months
	Credit score	Assessed at baseline, 6, and 12 months
	Financial Capability (knowledge, skills, practices, mindset) (45)	Every six months: baseline, 6, 12, 18, 24 months
Mental health	Anxiety – moderate–severe: score ≥ 10 on GAD-7 (66, 67)	Quarterly surveys
	Hope/ future orientation (68, 69)	Surveys at baseline, 6, 12, 18, 24 months
Physical health	General health (70); fatigue	Surveys at baseline, 6, 12, 18, 24 months
Secondary exposure		
Intervention dose	Engagement with optional intervention components (peer groups and mentoring)	Study monitoring forms
Covariates/Mediators		
Demographics	Age, gender identity, housing/living situation, household membership, income, employment	Quarterly surveys
Strengths and assets	Resilience (71); self-esteem; Black identity (72); decision-making and goal-setting	Frequency varies – six-month and annual surveys
Social and structural contextual factors	Experienced discrimination (73); alcohol and substance use (74); social support (75, 76); social cohesion (77, 78); incarceration; relationship violence (79); trauma (80); prosocial involvement; food security	Frequency varies - quarterly; six-months; and annual surveys

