#### Primary analyses

Our primary analyses will test the hypothesis that GI will improve all primary outcomes at 12 months (H1). Specifically, we hypothesize that participants receiving GI in phase I will have (a) greater increases in investments in their future; (b) greater decreases in depressive symptoms, and (c) larger reductions in unmet need for MH and SRH services at 12 months than the no-GI arm.

We will use generalized estimating equations (GEE) to test our primary hypotheses and this analysis will follow an intent-to-treat approach by including all randomized participants. Our primary interest is to estimate the marginal or population-average effects of intervention participation on these primary outcomes rather than the effect for a hypothetical average subject (91). Moreover, within-subject outcome correlations are considered nuisance parameters rather than quantities of interest to be modeled explicitly. Accordingly, GEE can be used to estimate the marginal effects using difference-in-differences (DID) comparisons of post-baseline (follow-up) measurements of the Phase 1 GI group with the comparison arm in the main trial Phase. Since our primary outcomes are dichotomous, these models will employ a logit link and assume a binomial distribution. For each model, we will include indicators for study arm, time and the interaction between study arm and time to examine the relative change in outcomes for each arm during Phase 1. If changes in each outcome do not follow a linear trend, we will explore alternative relationships including polynomial and spline terms. Alpha (α) will be set at 0.05 for each of our planned comparisons. Any additional post-hoc comparisons (e.g., paired comparisons of groups at each time point) will maintain a nominal alpha of 0.05 through the use of simulation-based stepdown multiple comparison methods (92).

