This study has some limitations. Little is known about the unintended consequences of GI among emerging adults, but we are gathering information, such as social harms, to shed light on potential limitations of GI. The BEEM Project uses residence in low-income census tracts (or marginal housing status) as a proxy for low-income status since many young people do not know their household’s income. This may result in greater heterogeneity in baseline income levels than directly measurement of household income. However, we will assess other indicators of income and socioeconomic status (receipt of public benefits, maternal education, income earned) and can adjust for baseline differences if treatment arms are imbalanced. Selection bias may be introduced due to self-selection into the non-GI intervention components (financial mentoring and peer discussion groups). We will adjust for these differences across sub-strata in our analysis by using causal inference methods. The ITS analysis of H3 will be subject to the usual threats if other time shocks occur, such as changes in local social determinants of health outside of study control; these conditions will be monitored to assist in results interpretation. Because this study is set in two cities in California, findings may not be generalizable outside of urban areas in California. Finally, the temporary one-year nature of our GI intervention may result in smaller effects than would an ongoing GI program supporting BEA throughout their entire emerging adulthood period from age 18 to 24.

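### A baseline significance test decides whether the primary analysis is reweighted; after randomisation the test is uninformative, and chance could trigger it in many, possibly most, trials

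*Protocol article*

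**What the plan says.** Under Preliminary analyses, the article describes the sample, checks the arms for imbalance, and then sets a condition: "If arms differ significantly at baseline on one or more covariates or if imbalances in arms occur due to differential loss to follow-up". When it is met, "we will use causal modeling methods (e.g., inverse probability weighting, targeted maximum likelihood estimation) to balance distributions", with a marginal effect under balanced arms as the stated target.

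Under Primary analyses the default is stated: "We will use generalized estimating equations (GEE) to test our primary hypotheses", with a logit link, terms for arm, time and their interaction, and a population-average effect as the target. The same section lets baseline demographic, psychosocial and contextual covariates into the model when they improve QIC.

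Randomization and treatment allocation says that allocation is balanced on gender, age group and city. The Primary analyses section does not name these three as fixed model terms.

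The limitations part of the Discussion says of income and socioeconomic indicators that the team "can adjust for baseline differences if treatment arms are imbalanced". That also ties adjustment to observed imbalance, but it mentions no significance test.

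**The concern.** Arms formed by randomisation differ at baseline only by chance. A significance test of those differences asks a question whose answer is already known. It also measures the wrong thing. Whether adjustment helps depends on how strongly a covariate predicts the outcome. A non-significant imbalance on a strong predictor can matter, while a significant one on an irrelevant variable does not.

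The rule still lets that test choose the form of the primary analysis, and one significant covariate is enough. Whether the main estimate is weighted, and with what standard error, is known only after the data have been inspected. QIC selection then makes the covariate set data-dependent as well. At stake are the pre-specification of the primary analysis and the precision that a fixed prognostic adjustment would give.

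**Working it through.** The article gives no figure for how often the baseline trigger would fire, so there is none to reproduce. The rate can be derived.

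**Number of covariates**
- Table 1, demographics ("Age, gender identity, housing/living situation, household membership, income, employment"): 6.
- Table 1, strengths and assets ("Resilience (71); self-esteem; Black identity (72); decision-making and goal-setting"): 4.
- Table 1, social and structural factors, from experienced discrimination to food security: 9.
- Table 1 total: 6 + 4 + 9 = 19. Without age and gender, which the randomisation balances: 17.
- The covariate paragraph under Secondary outcomes adds education, partnerships and financial supports: 19 + 3 = 22. Without age and gender: 20.

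**Alpha of each baseline test.** None is given. I assume 0.05 two-sided, the only alpha in the article ("Alpha (α) will be set at 0.05 for each of our planned comparisons"), and show 0.01 and 0.10 as the range.

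**Independent covariates.** P(at least one significant) = 1 − (1 − α)^k.
- k = 17: 1 − 0.95^17 = 0.582
- k = 19: 1 − 0.95^19 = 0.623
- k = 20: 1 − 0.95^20 = 0.642
- k = 22: 1 − 0.95^22 = 0.676
- The 50% line lies between k = 13 (0.487) and k = 14 (0.512).
- k = 20 at other alphas: 1 − 0.99^20 = 0.182; 1 − 0.90^20 = 0.878.

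**Correlated covariates.** Simulation of equicorrelated normal test statistics, counting any |Z| > 1.96:

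| Common correlation | k = 20 | k = 22 |
|---|---|---|
| 0.1 | 63% | 66% |
| 0.2 | 59% | 62% |
| 0.3 | 54% | 57% |
| 0.4 | 48% | 51% |
| 0.5 | 42% | 44% |

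**Does the rule distort the error rate?** It was simulated with no treatment effect: 300 participants 1:1, 20 covariates of which five were prognostic, a binary outcome at one time point, and 10,000 runs per scenario. If any baseline t-test gave p < 0.05, IPW with robust standard errors was used; otherwise the unadjusted difference was used.
- The trigger fired in 59% to 65% of runs.
- Type I error of the two-stage rule was 4.1% to 5.4% when weighting on the significant covariates, and 3.1% to 4.3% when weighting on all 20. Never adjusting gave 4.9% to 5.4%.
- A separate check put the two-stage rule at about 2% to 4%.

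**Does it cost precision?** In that separate check, always weighting on the prognostic covariates cut the standard deviation of the effect estimate by about 13% to 18% against no adjustment, and by about 10% to 14% against the two-stage rule. As variance, the latter is 1 − 0.90² = 19% to 1 − 0.86² = 26%.

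These simulations omit repeated measures, attrition and TMLE. Their prognostic strengths are assumed, so they show direction rather than a forecast for this trial.

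**The case against.** The strongest defence has five parts.

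1. **A reader might infer that the rule inflates false positives.** The article does not support that, and the simulations point the other way: error near 5% or mildly conservative. They do not cover an analyst who chooses between estimators after seeing results, but the investigators and the methodologist are blinded to allocation. This part stands. The complaint is about pre-specification and precision.
2. **A reader might infer that the GEE is discarded.** IPW can be applied as weights inside the GEE, and both sections aim at a marginal effect. Only TMLE would literally replace the GEE. This stands, although the estimate and standard error change either way.
3. **A reader might infer that significance also selects the weighting covariates.** The text makes significance the trigger and does not say which variables enter the weights. That inference is dropped.
4. **Prognostic covariates are not ignored.** QIC can admit them whatever the baseline tests show, and the arm-by-time model deals with baseline differences in the outcome itself. This is true, but QIC selection is a further data-driven step and fixes nothing in advance.
5. **The trigger rate rests on assumptions.** No test, alpha or tested list is given, and Table 1 heads these rows as covariates or mediators. This stands, so many, possibly most, is the right strength.

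The differential-loss half of the condition is a legitimate and separate matter. The choice between IPW and TMLE may be left to an analysis plan not shown here. Neither is criticised.

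**Conclusion.** The point holds in limited form. The article itself states a rule under which a significance test of chance differences determines the primary analysis, and that test carries no information on whether adjustment is useful. This is a stated rule, not detail left to another document.

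With 17 to 22 independent covariates at an assumed 0.05, the rule would be triggered in 58% to 68% of correctly randomised trials. The rate falls below half with 13 or fewer independent tests, with 20 tests at a common correlation of 0.4 or more, or at a strict alpha. The objection to the rule does not need the rate to exceed 50%. I read the word significantly as statistical significance, its ordinary sense here.

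The consequence is a primary analysis that is not fixed in advance, compounded by QIC selection, and a probable loss of precision against a fixed prognostic adjustment. The article does not show that IPW or TMLE would be biased, and inflation of type I error is not shown. The change is worth making, but the concern is not grave.

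**What to change.** - In Preliminary analyses, delete the baseline-significance trigger and keep the baseline table descriptive.
- In Primary analyses, delete the admission of covariates by QIC. Removing the trigger alone would still leave the covariate set open.
- State one primary analysis, used whatever the baseline table shows: the GEE with gender, age group and city plus a short list of prognostic baseline covariates named before unblinding.
- Standardise its result to a marginal effect, because covariate adjustment on the logit scale otherwise changes the population-average quantity that the article targets. Weighting or TMLE with the same named covariates, always applied, would serve equally well.
- Handle loss to follow-up separately, with its predictors fixed in advance and no significance test deciding whether it is used.
- Align the limitations sentence in the Discussion with this.

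The cost is analysis wording and slightly more analysis work. Recruitment, surveys and sample size are untouched.

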#### Primary analyses

Our primary analyses will test the hypothesis that GI will improve all primary outcomes at 12 months (H1). Specifically, we hypothesize that participants receiving GI in phase I will have (a) greater increases in investments in their future; (b) greater decreases in depressive symptoms, and (c) larger reductions in unmet need for MH and SRH services at 12 months than the no-GI arm.

We will use generalized estimating equations (GEE) to test our primary hypotheses and this analysis will follow an intent-to-treat approach by including all randomized participants. Our primary interest is to estimate the marginal or population-average effects of intervention participation on these primary outcomes rather than the effect for a hypothetical average subject (91). Moreover, within-subject outcome correlations are considered nuisance parameters rather than quantities of interest to be modeled explicitly. Accordingly, GEE can be used to estimate the marginal effects using difference-in-differences (DID) comparisons of post-baseline (follow-up) measurements of the Phase 1 GI group with the comparison arm in the main trial Phase. Since our primary outcomes are dichotomous, these models will employ a logit link and assume a binomial distribution. For each model, we will include indicators for study arm, time and the interaction between study arm and time to examine the relative change in outcomes for each arm during Phase 1. If changes in each outcome do not follow a linear trend, we will explore alternative relationships including polynomial and spline terms. Alpha (α) will be set at 0.05 for each of our planned comparisons. Any additional post-hoc comparisons (e.g., paired comparisons of groups at each time point) will maintain a nominal alpha of 0.05 through the use of simulation-based stepdown multiple comparison methods (92).

Though GEE estimates are consistent even if the correlation structure is mis-specified, GEE’s statistical efficiency improves as the working correlation structure more closely approximates the actual correlation structure (93, 94): therefore, various correlation structures suitable for the study’s design will be considered (e.g., exchangeable; M-dependent) (94). The QIC statistic will be used to select the final correlation structure (95). Additional covariates, including baseline demographic characteristics, psycho-social covariates and social and structural contextual factors will be included if they improve QIC. Robust Huber-White “sandwich” standard errors will be used to obtain correct inferences even if the chosen correlation structure remains slightly misspecified. GEE case deletion diagnostics (e.g., DFBetas, Cook’s D) will be used to investigate whether influential cases are present; if so, results will be reported with and without influential cases included (96).

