#### Sample size estimation

Power analyzes were generated using the equation defined by Diggle et al. (97) to compute minimum detectable effect sizes for the primary analyses to address Hypotheses 1a-1c. The study will begin with 300 participants equally allocated to two study groups. Assuming 25% attrition over 12 months, we anticipate an average of 4.3 observations from 300 participants will be available for analysis of investments in the future and mental health outcomes and an average of 5.7 observations for analysis of unmet service need outcomes. Assuming *α* = 0.05 and power = 0.80, with four highly correlated post-baseline measurements [intraclass correlation (ICC) = 0.20–0.80] and a range of outcomes for waitlist control participants (change in each outcome between 5 and 40%), we will have sufficient power to detect differences as low as 5.7–10.7% for increase in enrollment in educational or training programs and decrease in depression, and 4.5–10.6% for decrease in unmet service need, respectively, in the intervention arm compared to waitlist controls.

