#### Secondary analyses

We will determine if BEA receiving GI in Phase 1 who opt-in to peer discussion groups and financial mentoring will have larger increases in odds of investment in the future, larger declines in odds of depressive symptoms and larger declines in odds of unmet mental and sexual health service needs at 12 months compared to those who did not opt into these support programs (H2). We will use the same modeling approach as described above for H1 used to test H2 except that analysis will be restricted to a single arm of the study (those receiving GI in phase I or those receiving GI in phase II).

As in our preliminary analyses, we will employ causal inference methods to adjust for any differences between sub-strata [e.g., individuals who do or do not opt in to financial mentoring or peer discussion groups at baseline or due to differential loss to follow-up]. As in our primary analyses, we will use logistic GEE to model our dichotomous outcomes, and continuous GEE specifications for continuous measures. We will test H2 via DID comparison of post-baseline measurements in the Phase 1 GI group during Phase 1 (as in H1). All comparisons for secondary analyses (H2 through H4) will be tested at *α* = 0.05 per comparison.

We will test (H3)–BEA receiving GI in Phase 1 will not experience a significant decline in odds of enrollment in educational or training programs, a significant increase in odds of depression or a significant increase in odds of unmet mental and sexual health service needs following removal of the GI (between month 12 and 24)–using an interrupted time series (ITS) approach. For these ITS analyses, we will include indicators for phase, time and the interaction between phase and time to examine the slope in each outcome during Phase 1, the presence of an immediate change in each outcome after removal of GI (level effect), as well the change in slope for each outcome during Phase 2 (slope). If changes in outcomes do not follow a linear trend, we will explore alternative relationships including polynomial and spline terms.

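### The H1 target is a marginal effect, but covariates kept by QIC turn the logit-GEE coefficient into a covariate-conditional one, and standardisation is not planned when arms are balanced

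*Protocol article*

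**What the plan says.** All references are to the Analyses part of the protocol article.

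- **Target.** Primary analyses: "Our primary interest is to estimate the marginal or population-average effects of intervention participation on these primary outcomes". This is set against a subject-specific effect: "rather than the effect for a hypothetical average subject".
- **Model.** Same section: "these models will employ a logit link and assume a binomial distribution", and "we will include indicators for study arm, time and the interaction between study arm and time to examine the relative change in outcomes". The interaction coefficient is a log ratio of odds ratios.
- **Covariates.** Same section: "Additional covariates, including baseline demographic characteristics, psycho-social covariates and social and structural contextual factors will be included if they improve QIC". Nothing ties the four primary outcomes to one common covariate set.
- **Marginal methods.** Preliminary analyses names inverse probability weighting and targeted maximum likelihood as routes to the marginal effect it wants. It invokes them only if arms differ at baseline or become imbalanced through differential loss to follow-up.
- **Planning scale.** Sample size estimation gives the detectable effects for H1 as "differences as low as 5.7–10.7% for increase in enrollment in educational or training programs" and for the decrease in depression, with 4.5–10.6% for unmet service need.

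**The concern.** GEE averages over the correlation between repeated measurements on a person. It does not average over covariates placed in the mean model. With arm, time and their interaction alone, the logit coefficient is population-average, as the protocol intends. When covariates enter, the coefficient compares the arms at fixed covariate values.

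On the logit scale these two quantities differ even when the covariates are perfectly balanced between arms. The protocol's usual case, balanced arms with QIC-selected covariates, is thus the one in which it has no stated step back to its own target.

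What is at stake is the size of the reported effect. If the adjusted coefficient is presented as the population-average effect, it overstates that effect on the log-odds scale. The overstatement varies by outcome, because it depends on how prognostic the retained covariates are.

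**Working it through.** The protocol gives no odds ratio that could be reproduced. Its planning range of 5.7–10.7% is used here only to place the examples on a realistic scale.

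**Inputs**
- Link, tested term and covariate rule: Primary analyses.
- Arm rates: 40% v 30% (illustrative), and 30% v 40.7%, which is the top of the planned range (10.7 points) on an assumed control rate of 30%.
- Combined SD of the retained covariates on the logit scale, s: 0.5, 1.0, 1.5 and 2.0. The protocol gives no value, so these are assumptions and a range is shown.
- Covariates are measured at baseline and are equally distributed in both arms.

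**Reduction to month 12.** If both arms have the same baseline rate, as randomisation gives in expectation, the baseline odds ratio is 1. The ratio of odds ratios then equals the month-12 odds ratio.

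**Formulas**
- Marginal OR = [p1/(1−p1)] / [p0/(1−p0)].
- Conditional OR = exp(a1 − a0), where each a solves: mean of expit(a + sZ) = p, with Z standard normal (Gauss–Hermite integration).

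**Example 1: p0 = 0.40, p1 = 0.30**
- Marginal OR = (0.30/0.70)/(0.40/0.60) = 0.4286/0.6667 = 0.643; log OR = −0.442.
- s = 0.5: a0 = −0.429, a1 = −0.895; exp(−0.466) = 0.628.
- s = 1.0: a0 = −0.490, a1 = −1.018; exp(−0.529) = 0.589.
- s = 1.5: a0 = −0.572, a1 = −1.188; exp(−0.615) = 0.540.

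The difference is 10 percentage points in every row.

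**Example 2: p0 = 0.30, p1 = 0.407**
- Marginal OR = (0.407/0.593)/(0.30/0.70) = 0.6863/0.4286 = 1.60; log OR = 0.471.

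| s | Conditional OR | Log OR | Excess over marginal log OR |
|---|---|---|---|
| 0.5 | 1.64 | 0.497 | 5% |
| 1.0 | 1.76 | 0.564 | 20% |
| 1.5 | 1.93 | 0.656 | 39% |
| 2.0 | 2.15 | 0.764 | 62% |

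For control rates of 20% to 50% and the same 10.7-point effect, the excess is about 5% (s = 0.5), 17–21% (s = 1.0), 35–41% (s = 1.5) and 57–65% (s = 2.0).

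**Null and direction.** If p1 = p0 then a1 = a0 for every s, so the conditional OR is 1 whenever the marginal OR is 1. Because a increases with p, the two always lie on the same side of 1. With equal baselines this covers H1.

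**After the fix.** Averaging the fitted probabilities over the covariate distribution recovers p0 and p1 in every row: 10 points or OR 0.643 in example 1, 10.7 points or OR 1.60 in example 2, whatever s is.

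**The case against.** The strongest reply is that the protocol uses marginal in the ordinary GEE sense, as opposed to a random-effects model, and that a logit GEE meets that sense. This stands for the model without covariates: the logit link on its own contradicts nothing. It does not cover the adjusted model, because the text asks for a population-average effect and covariate adjustment on the logit scale moves away from it.

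A second reply is that the reported effect measure is normally left to an analysis plan, which is not shown. It is true that the article does not name the reported measure. But the target, the link, the covariate rule and the condition for using marginal methods are all written down, and they do not fit together. That is more than missing detail.

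Third, the size rests on assumed covariate strength. This is correct. At an SD of 0.5 the shift is small (0.643 to 0.628).

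Two stronger readings are tempting and are not supported:
- A reader might infer that planning in percentage points and testing on the logit scale is itself an error. It is common practice, and a given control rate maps one onto the other.
- A reader might infer that H2 and H4 could come out with the wrong sign, because self-selected groups may start at different levels and the two scales can then disagree. Secondary analyses states these hypotheses in odds (for H2: "will have larger increases in odds of investment in the future"), so the logit interaction is on their own scale. It also plans causal adjustment for differences between the opt-in strata.

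**Conclusion.** The concern holds for H1 and is limited to the size of the effect. The stated covariate rule departs from the stated target whenever QIC keeps a prognostic covariate and the arms are balanced. The adjusted odds ratio is then further from 1 than the marginal one. For 40% v 30% it is 0.628 to 0.540 against 0.643 at assumed SDs of 0.5 to 1.5; at the top of the planned range on a 30% control rate, the log odds ratio is 5% to 62% too large at SDs of 0.5 to 2.0. The SDs are not in the document, so the actual shift is unknown. It can also differ between the four primary outcomes, since each may keep its own covariates.

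Non-collapsibility does not invalidate the H1 test or change its direction. No sign error is claimed for H2 or H4. The point should be corrected before analysis, because the remedy is cheap and uses the model already planned.

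**What to change.** Add to the primary analysis: when covariates are retained, the H1 month-12 effect is obtained by standardisation.

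1. Fit the planned GEE with the retained covariates.
2. For every randomised participant, compute the fitted month-12 probability twice, with arm set to Phase 1 GI and to waitlist, holding covariates at their baseline values.
3. Average over all randomised participants and contrast the two averages. Report the risk difference (the scale used in Sample size estimation), the marginal odds ratio, or both.
4. Give a delta-method interval based on the robust covariance, or a bootstrap interval that resamples participants. Do this within each imputed data set and combine, since multiple imputation is already planned.
5. Keep the conditional odds ratio as supportive, and list the covariates kept for each outcome.

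For H2 and H4, leave the odds scale as stated. A standardised risk difference may be shown alongside as supportive.

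The cost is a few sentences of analysis text and one post-estimation step, so slightly more programming. No new data and no change to the sample size are needed.
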